# Safety and effectiveness of a Patient Blood Management (PBM) program in surgical patients - the study design for a multi-centre prospective epidemiologic non-inferiority trial

**DOI:** 10.1186/s12913-014-0576-3

**Published:** 2014-11-19

**Keywords:** Patient Blood Management, Red Blood Cell Transfusion Practice, Patient Safety, Anaemia, Clinical Outcome, Perioperative Care

## Abstract

**Background:**

Preoperative and hospital-acquired anaemia is common among surgical patients. It is associated with an increased risk of morbidity and mortality and a strong risk factor for allogeneic blood transfusions with their own inherent risks. Patient Blood Management (PBM) concepts aim to increase and preserve autologous erythrocyte volume and to optimise haemotherapy. They thus have great potential to benefit patients.

**Methods/Design:**

This prospective, multi-centre clinical trial tests the hypothesis that PBM programs are safe and effective in the care of adult surgical patients. Primary outcome is a composite endpoint of adverse events and in-hospital mortality.

**Discussion:**

This trial will determine whether the implementation of a PBM program is safe and effective in terms of clinical outcome compared to a pre-implementation cohort. This trial is registered at www.clinicaltrials.gov (NCT01820949).

## Background

Anaemia has a high prevalence among surgical patients as it is often preexisting, acquired and/or exacerbated during hospital stay [1,2]. It is associated with higher risks of morbidity and mortality and is also a major risk factor for allogeneic blood transfusions. The transfusion of allogeneic red blood cell (RBC) units is by itself also associated with increased morbidity and mortality due to infectious, immunological, pulmonary and thromboembolic complications [3-5]. Surely, adequate RBC transfusion is a life-saving medical intervention for those in need of it, but transfusion practice varies significantly when comparing hospitals and physicians, which implies that insecurity regarding adequate utilisation exists [6,7]. Additionally, serious blood supply challenges are imminent due to changing population demographics. Therefore, modifiable risk factors for transfusion such as anaemia should be targeted and a rational use of RBC units and safe clinical transfusion practice is mandatory. The World Health Organisation encourages all member states to implement Patient Blood Management (PBM) programs employing multiple combined strategies to increase and preserve autologous erythrocyte volume in order to minimise unnecessary exposure to RBC transfusions [8]. Early detection and appropriate treatment of anaemia, multidisciplinary concepts designed to maintain haemoglobin concentration, to optimise haemostasis, and to minimise blood loss shall be thrived for in an effort to improve patient outcome and ensure adequate use of scarce resources [9,10].

Several public-based PBM initiatives are in progress, e.g. in Australia, to optimise utilisation of RBC concentrates [8,11]. However, none of these initiatives is designed to provide scientific data in terms of safety issues. Thus, a large study with robust and relevant clinical endpoints is required. The object of this study is to demonstrate that the implementation of a PBM program is safe.

## Methods

### Trial design

This is a prospective multi-centre controlled epidemiologic non-inferiority trial with an approximated population of 100,000 patients undergoing surgical procedures. A patient-focused and evidence-based PBM program has been implemented in four German University Hospitals. Different time slots for control, implementation and study phases according to a non-randomised stepped wedge trial design were allocated for control, implementation and intervention periods.

### Participants

Four German university hospitals are participating in the study: Frankfurt, Bonn, Kiel, Muenster. The PBM program includes all patients undergoing surgical procedures ranging anywhere from: orthopaedic and visceral surgery, general surgery, cardiothoracic surgery, trauma, otorhinolaryngology, gynecology and obstetrics, urology, oral and maxillofacial surgery, vascular surgery, and neurosurgery to increase applicability of the evidence obtained during this trial. Exclusion criteria are: <18 years, ophthalmologic or dermatologic or outpatient surgery. If a patient has multiple hospital admissions during the study period, the first hospital stay will be analysed.

The control group will be composed of the patients treated according to the standard protocol in charge before implementation of the PBM program. A period of three months was allowed for the implementation of the PBM components. Patients treated after implementation will be allocated to the PBM cohort until July 2015.

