## Statistics

### Sample size and power calculation

According to preliminary data, the composite endpoint has an approximate incidence of 10%. A difference of 0,5% is set as the non-inferiority margin as this can be seen as the natural standard deviation. The level of significance of non-inferiority is determined be α = 2.5%. This is consistent with a two-sided 95% confidence range of 1 + α = 95% for the difference in the composite endpoint. A power of 1 + β = 80% is sought. As the number of patients treated in each of the four university hospitals vary, an exact sample size calculation is not possible to this date. However, we expect approximately 100,000 participating patients.

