### Statistical analysis

The primary aim is to prove non-inferiority of the intervention (PBM) cohort when compared with the control cohort stratified by center. The primary composite endpoint will be registered electronically by analysis of ICD-10 diagnoses and will be exported to a data base. It will be analysed with a one-sided Mantel-Haenszel test with significance level of α =2.5% for the odds ratio resulting in H0: OR ≥ OR* vs. H1 OR < OR* with OR* being derived from the incidence in the control cohort and an incidence rate of the PBM cohort which is increased by the non-inferiority margin of 0.5%. As secondary analysis, we will analyse two-sided 95% confidence interval for the difference in the frequency of the composite safety endpoint as well as for the odds ratios and the single components of the composite endpoint. Additionally, the influence of covariates, e.g. the calendar year, concomitant diseases, the asynchrony of the study periods at different sites will be assessed statistically. Should there be a significant influence on the incidence of the composite endpoint, the Mantel-Haenszel test will be supplemented with a respective multivariate approach accounting for covariates.

Secondary endpoints will be compared with a two-sided Wilcoxon-Mann–Whitney test using a significance level of α =5%. A subgroup analysis will assess if there is some bias from not excluding patients with multiple hospital stays for surgical intervention during the study period. A further subgroup analysis will assess if there is a difference of safety between a) elective patients who will receive preoperative haemoglobin optimisation compared to b) anemic patients who will not undergo preoperative haemoglobin optimisation due to failed postponement of surgery in case of surgical urgency or non-elective surgery, respectively.

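### The first-stay rule, read as one window over the study, takes patients with a control-phase stay out of the PBM cohort only; if they carry above-average risk, the comparison shifts toward non-inferiority

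*Protocol article*

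**What the plan says.** The Participants section of the protocol article sets the unit of analysis: "If a patient has multiple hospital admissions during the study period, the first hospital stay will be analysed". The same section fixes the order of the cohorts: "The control group will be composed of the patients treated according to the standard protocol in charge before implementation of the PBM program", and "Patients treated after implementation will be allocated to the PBM cohort until July 2015". Between them, "A period of three months was allowed for the implementation of the PBM components". The Trial design section describes "Different time slots for control, implementation and study phases according to a non-randomised stepped wedge trial design".

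Two planned analyses bear on the point, both under Statistical analysis. One concerns repeat stays directly: "A subgroup analysis will assess if there is some bias from not excluding patients with multiple hospital stays"; how it will be done is not stated. The other examines covariates, naming calendar year, concomitant diseases and site asynchrony as examples, and adds a multivariate analysis to the Mantel-Haenszel test if they prove significant. An earlier stay is not among the named covariates.

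The yardstick is in the sample-size section: "A difference of 0,5% is set as the non-inferiority margin", with an expected incidence of about 10%, one-sided alpha of 2.5% and about 100,000 patients.

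**The concern.** A rule of one stay per patient looks neutral. It is not neutral when the two cohorts are consecutive periods at the same hospitals. With one window over the whole study, a patient operated on in both phases always enters as a control. A PBM-phase patient is kept only if there was no control-phase stay; a control patient faces no such check against an earlier period.

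Repeat-surgery patients (revisions, complications, cancer, vascular disease) plausibly differ in risk from patients seen once. If their risk is higher, the PBM cohort is healthier by selection. For a safety claim resting on non-inferiority that is the anti-conservative direction, and with a margin of half a percentage point a small difference in case mix matters.

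**Working it through.** **Plan's own figure.** The article gives no number for returning patients, so there is none to reproduce on this point. Its 100,000 is an expectation; the article says an exact calculation was not possible. For reference, the stated inputs give (1.960 + 0.842)² × 2 × 0.10 × 0.90 / 0.005² ≈ 56,512 per cohort, or 113,024 in total at equal allocation. Nothing below depends on that difference.

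**Inputs from the article.** Incidence 10%; margin 0.5 points; one-sided alpha 2.5%; total about 100,000.

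**Assumed inputs.** *s*, the share of PBM-phase patients who also had a control-phase stay: 3%, 5%, 10%. *r*, the event risk of those patients in the PBM phase: 8% to 20%. Cohorts of 50,000 each.

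**Step 1: shift in PBM incidence with no PBM effect.** Removing share *s* at risk *r* from a population with overall risk 10% leaves (0.10 - s·r)/(1 - s). The shift is that value minus 0.10. For s = 5%, r = 15%: (0.10 - 0.0075)/0.95 = 0.09737, a shift of -0.26 points.

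| s | r = 8% | r = 10% | r = 12% | r = 15% | r = 20% |
|---|---|---|---|---|---|
| 3% | +0.06 | 0 | -0.06 | -0.15 | -0.31 |
| 5% | +0.11 | 0 | -0.11 | -0.26 | -0.53 |
| 10% | +0.22 | 0 | -0.22 | -0.56 | -1.11 |

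A shift equal to the whole margin needs r = 0.10 + 0.005(1 - s)/s: 26.2% at s = 3%, 19.5% at s = 5%, 14.5% at s = 10%.

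**Step 2: error at the margin.** The standard error of the difference is √(2 × 0.10 × 0.90 / 50,000) = 0.190 points. If PBM is truly 0.5 points worse, the chance of declaring non-inferiority is Φ(-shift/0.190 - 1.96). No shift gives 2.5%. A shift of -0.26 gives Φ(0.263/0.190 - 1.96) = 28%. A shift of -0.06 gives about 5%; a shift of +0.22 gives about 0.1%.

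**Step 3: does selecting within each phase remove the bias?** A simulation with no PBM effect gave each person an admission rate and an event risk that could be correlated. With a correlation of 0.6 and two 12-month phases, about 10.6% of PBM-phase patients also had a control-phase stay.

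| Phase lengths (control / PBM) | Control | PBM, first stay in phase | PBM, first stay in study |
|---|---|---|---|
| 12 / 12 months | 11.2% | 11.2% | 10.7% |
| 6 / 18 months | 11.3% | 11.1% | 10.9% |

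With equal phases, the per-phase rule removes the bias. With unequal phases it leaves about 0.2 points, because a longer window dilutes frequent attenders. With zero correlation there was no bias. With a correlation of -0.3 and equal phases, the single-window rule gave 6.3% in control against 6.4% in PBM, so the sign reverses.

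**The case against.** **The window is not defined.** The article does not say that the rule spans the whole study. Trial design uses the word *study* for the intervention phase, and Statistical analysis speaks of study periods in the plural when it discusses the sites. A per-phase rule is therefore possible and would largely remove the asymmetry. This stands, but the rule itself refers to one period and one first stay, so a single window is the natural reading. If a per-phase rule was meant, the text should say so.

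**The direction is not documented.** A reader might infer that the rule does bias the trial toward non-inferiority. The article does not support that. It gives no return share and no risk for returning patients. Everyone removed survived the earlier stay, and some second stays will be planned staged procedures at ordinary or low risk. This stands in full: sign and size are unknown.

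**The authors planned a check.** A reader might also infer that the multiple-stay analysis cannot detect the problem. Its content is not given, so that goes too far. What can be said is that one obvious form, dropping everyone with more than one stay, would not do. It does not restore the missing PBM patients, and it selects on later return: a patient who dies in the first stay can never be dropped.

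**Covariate adjustment may help.** Comorbidity is a likely route by which returning patients differ, and it is named. The adjustment is conditional on significance, however, and only supplements the primary test.

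**The depletion is limited.** Patients who return only within the PBM phase remain through their first stay there, and later stays within a phase are dropped in both cohorts. This is correct; the asymmetry concerns only patients with a stay in both phases.

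**Conclusion.** The point holds conditionally. On the natural reading, the selection rule treats the cohorts differently, and this follows from the text alone. Whether it biases the result, and which way, depends on the share and risk of patients with stays in both phases, which the article does not give. Over the assumed ranges the shift in PBM incidence runs from +0.22 to -1.11 points, so it may be negligible, may work against PBM, or may exceed the 0.5-point margin. The 28% error belongs to one scenario (5% of patients at 15% risk, 50,000 per cohort) and is not an estimate for this trial. Because the rule defines the primary analysis set and no planned analysis clearly corrects it, it should be settled before the data are analysed.

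**What to change.** - **Rule.** State it as the first eligible stay within each phase (control, PBM) at each centre, over phase windows of comparable length or with the same look-back washout in both cohorts. A patient may appear once in each cohort.
- **Primary analysis.** Keep the stratification by centre and use a patient-clustered variance.
- **Reporting.** Give the number of patients with stays in both phases and their event rate, so that the table above can be replaced by observed values.
- **Sensitivity.** Specify the multiple-stay analysis as one of all eligible stays, clustered by patient.

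The cost is small. The present rule already requires a patient's stays to be linked, so this changes data extraction and variance estimation and leaves care untouched. The downside is that some patients appear in both cohorts, so the plain Mantel-Haenszel variance, which assumes independence, must be replaced or supplemented. Trimming windows to comparable length, or applying a washout, may also cost some patients.

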### Management

For consistent implementation regular teaching sessions were held at the beginning of the program and are repeated every six months. The focus is on clinical practice, outcome and safety issues in order to increase knowledge on PBM and awareness of the clinical implications of anaemia and the need for alternatives to transfusion. The new program is additionally promoted through hand outs, posters, checklists and web-based information among health care providers and patients.

Our PBM program has three main pillars:**Preoperative optimisation of haemoglobin levels:**

The preoperative detection, evaluation and therapy of anaemia diagnosis and treatment focuses specifically on those patients (aged 18 years and older) scheduled for elective surgery. Figure 1 shows the work-flow used at the University Hospital Frankfurt. Surgeries associated with a risk for transfusion >10% were identified by retrospective analysis of hospital data from 2011 with the hospital-information system Agfa ORBIS. Patients scheduled for elective surgery falling in that spectrum are screened and treated at the earliest possibility according to NATA and SABM recommendations if surgery can be postponed for at least four days (Figure 1) [12]. Iron deficiency anaemia (IDA) is treated with intravenous iron. Anaemic patients are suggested to be scheduled for both haematological and/or gastroenterological consultations for further diagnostics and optimal treatment of anaemia in cases where iron deficiency anaemia is unlikely.

**Figure 1 Fig1:**
[figure not shown]
**Algorithm for the detection, evaluation and management of anaemia at the University Hospital Frankfurt.**

b)**Standardisation of transfusion practice according to evidence-based guidelines:**

Lectures on transfusion triggers according to the Cross-Sectional Guidelines for Therapy with Blood Components and Plasma Derivatives of the German Medical Association [13]. The strict enforcement of guideline-based transfusion triggers for surgical patients is supported by checklists attached to each RBC and/or during electronic documentation of the indication for RBC in patient’s record (Figure 2) and during the perioperative process (Figure 3).

**Figure 2 Fig2:**
[figure not shown]
**Transfusion trigger checklist.**

**Figure 3 Fig3:**
[figure not shown]
**Perioperative patient blood management checklist.**

c)**Alternatives to transfusion, and blood-sparing techniques:**

This part of the PBM program comprises a broad use of the cell saver system in defined subgroups of patients, temperature management, point-of-care diagnostics, optimised coagulation management, and restrictive blood sampling [14].

In support of the strategies above, a PBM Checklist was introduced to guide physicians through the perioperative process (Figure 3).

## Endpoints

### Primary efficacy endpoint

Primary endpoints are the following composite endpoints: in-hospital myocardial infarction, stroke, acute renal failure, death of any cause, pneumonia and sepsis until discharge from hospital in patients before and after implementation of PBM program.

### Secondary endpoints

Length of stay on the intensive care unitTotal hospital stayQuantitative utilisation of allogeneic RBC units, platelet concentrates, other blood products

### Data recording

The efficacy endpoints will be monitored by means of the hospital-information system Agfa ORBIS, where the relevant diagnoses are encoded based on the ICD-10 system. All patient-related data will be analysed electronically and anonymised. The follow-up will last until discharge from the hospital.

### Ethics

The PBM program is in accordance with state of the art transfusion guidelines and current recommendations for preoperative haemoglobin optimisation. This prospective multi-centre controlled epidemiologic trial (non-inferiority) has been approved by the ethics committees of the University Hospital Frankfurt (Ref.: 380/12) and of all participating centers. Data collection is performed anonymously. All collected data will be kept confidential. This study will be performed in accordance with the revision of the Declaration of Helsinki (2013) [15]. Since implementation will affect all hospitalised patients, information and informed consent of individual patients will not be obtained.

## Statistics

### Sample size and power calculation

According to preliminary data, the composite endpoint has an approximate incidence of 10%. A difference of 0,5% is set as the non-inferiority margin as this can be seen as the natural standard deviation. The level of significance of non-inferiority is determined be α = 2.5%. This is consistent with a two-sided 95% confidence range of 1 + α = 95% for the difference in the composite endpoint. A power of 1 + β = 80% is sought. As the number of patients treated in each of the four university hospitals vary, an exact sample size calculation is not possible to this date. However, we expect approximately 100,000 participating patients.

### Statistical analysis

The primary aim is to prove non-inferiority of the intervention (PBM) cohort when compared with the control cohort stratified by center. The primary composite endpoint will be registered electronically by analysis of ICD-10 diagnoses and will be exported to a data base. It will be analysed with a one-sided Mantel-Haenszel test with significance level of α =2.5% for the odds ratio resulting in H0: OR ≥ OR* vs. H1 OR < OR* with OR* being derived from the incidence in the control cohort and an incidence rate of the PBM cohort which is increased by the non-inferiority margin of 0.5%. As secondary analysis, we will analyse two-sided 95% confidence interval for the difference in the frequency of the composite safety endpoint as well as for the odds ratios and the single components of the composite endpoint. Additionally, the influence of covariates, e.g. the calendar year, concomitant diseases, the asynchrony of the study periods at different sites will be assessed statistically. Should there be a significant influence on the incidence of the composite endpoint, the Mantel-Haenszel test will be supplemented with a respective multivariate approach accounting for covariates.

Secondary endpoints will be compared with a two-sided Wilcoxon-Mann–Whitney test using a significance level of α =5%. A subgroup analysis will assess if there is some bias from not excluding patients with multiple hospital stays for surgical intervention during the study period. A further subgroup analysis will assess if there is a difference of safety between a) elective patients who will receive preoperative haemoglobin optimisation compared to b) anemic patients who will not undergo preoperative haemoglobin optimisation due to failed postponement of surgery in case of surgical urgency or non-elective surgery, respectively.

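### The margin is a 0.5-point risk difference but the primary test is an odds ratio against a converted limit OR*, so the level for that margin is not fixed at 2.5%

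*Protocol article*

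**What the plan says.** In the protocol article, under Sample size and power calculation, the margin is absolute: "A difference of 0,5% is set as the non-inferiority margin". The expected incidence is about 10%. The one-sided alpha of 2.5% is linked there to a two-sided 95% interval "for the difference in the composite endpoint". About 100,000 patients are expected, and "A power of 1 + β = 80% is sought".

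Under Statistical analysis, the comparison is stratified by centre and the composite endpoint is decided by a "one-sided Mantel-Haenszel test with significance level of α =2.5% for the odds ratio". The null hypothesis is that the odds ratio is at least OR*, with "OR* being derived from the incidence in the control cohort and an incidence rate of the PBM cohort which is increased by" the 0.5-point margin. The 95% interval for the difference in frequency is a secondary analysis.

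The text does not say whether the control incidence behind OR* is pooled over the four hospitals or standardised to the centre mix of the comparison. It also does not say whether the sampling error of OR* enters the test.

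**The concern.** An odds ratio limit stands for a 0.5-point difference only at the incidence at which it was converted. Two things can then separate the test from the margin.

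- **Sampling error.** If OR* is computed from the control cohort's own data, it varies with the same data that enter the odds ratio. A test that treats it as a known constant uses the wrong standard error.
- **Centre mix.** The odds ratio is stratified, so differences in centre mix between the cohorts are removed from the estimate. If OR* uses one incidence pooled over the control cohort, that mix returns through the limit.

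Unequal mixes are plausible here. Under Trial design the hospitals have different time slots in a non-randomised stepped wedge, and the sample size section notes: "As the number of patients treated in each of the four university hospitals vary".

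The trial's main claim is safety. A level above 2.5% weakens that claim, and a level below it costs power.

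**Working it through.** **Inputs from the protocol.** Incidence 10%, margin d = 0.005, one-sided alpha 2.5% (z = 1.96), about 100,000 patients, four centres.

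**Assumptions.** 50,000 patients per cohort. Centre incidences either 10% everywhere or 6, 8, 12 and 14%. Centre shares as stated below. The protocol gives no value of OR* and no centre figures, so there is no stated OR* to reproduce.

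**1. OR\* depends on the incidence.** OR*(p) = [(p + d)/(1 − p − d)] / [p/(1 − p)].

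- At 6%: 1.089
- At 8%: 1.068
- At 10%: (0.105/0.895)/(0.10/0.90) = 1.056
- At 12%: 1.048

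**2. One stratum: the hypotheses agree, the standard error does not.** With OR* from the observed control incidence, log(OR/OR*) = logit(p_PBM) − logit(p_control + d). This is the risk-difference hypothesis on another scale. Take p_PBM = 0.105, p_control = 0.10 and n patients per cohort:

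- n × variance with OR* as a constant: 1/(0.105 × 0.895) + 1/(0.10 × 0.90) = 10.641 + 11.111 = 21.752
- n × variance with OR* as random: 10.641 + 0.09/(0.105 × 0.895)² = 10.641 + 10.191 = 20.832
- Ratio of standard errors: √(20.832/21.752) = 0.979
- Effective critical value: 1.96/0.979 = 2.00, so the level is about 2.26%

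**3. Power with equal centres and no true effect.**

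- Difference rule: SE = √(2 × 0.09/50,000) = 0.001897; 0.005/0.001897 − 1.96 = 0.675; power 75.0%.
- Odds ratio rule: log OR* = 0.0544. The SE used is √(22.222/50,000) = 0.02108; the actual SE is √(21.302/50,000) = 0.02064. (0.0544 − 1.96 × 0.02108)/0.02064 = 0.63; power about 73.6%.

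**4. How a pooled control incidence moves the limit.** Take incidences 6, 8, 12 and 14%.

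- Control shares 40/30/20/10%, PBM reversed. Pooled control incidence = 2.4 + 2.4 + 2.4 + 1.4 = 8.6%, so OR* = 1.064.
- Control shares 10/20/30/40%, PBM reversed. Pooled control incidence = 0.6 + 1.6 + 3.6 + 5.6 = 11.4%, so OR* = 1.050.
- In both cases the Mantel-Haenszel-weighted control incidence is 10%. At 10%, OR* = 1.064 corresponds to odds of 0.1111 × 1.064 = 0.1182, a risk of 10.57% and a margin of about 0.57 points. OR* = 1.050 gives odds of 0.1167, a risk of 10.45% and a margin of about 0.45 points.

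**5. Simulation.** At least 200,000 replicates per scenario. The odds ratio rule uses the Mantel-Haenszel log odds ratio with Robins-Breslow-Greenland variance against a pooled observed OR*. The difference rule uses Mantel-Haenszel weights. Level is at a true +0.5 points in every centre; power is at no true difference.

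| Scenario | OR rule: level | OR rule: power | Difference rule: level | Difference rule: power |
|---|---|---|---|---|
| All centres 10% | 2.2% | 73.5% | 2.5% | 75% |
| 6/8/12/14%, same mix in both cohorts | 2.1% | 73% | 2.4–2.5% | 76% |
| Mild shift, control 20/23/27/30%, PBM reversed | 1.65% | 68.5% | 2.5% | 74% |
| Mild shift, mirrored | 2.7% | – | 2.5% | – |
| Strong shift, control 40/30/20/10%, PBM reversed | 4.5% | – | 2.5% | – |
| Strong shift, mirrored | 1.2% | 54% | 2.5% | 66% |

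The two rules reach different verdicts in 9% to 12% of trials with no true effect in the two strong-shift cases, and in about 2% when the mix is the same in both cohorts. If OR* is taken from the centre-standardised control incidence, the odds ratio rule has a level of about 2.0% to 2.3% throughout.

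**The case against.** A reader might infer that the protocol contains two conflicting non-inferiority rules. It does not. The sample size section sets the margin and alpha for planning. The analysis section names one primary test, converts the margin openly, and labels the difference interval as secondary. With a single stratum the converted hypothesis is the risk-difference hypothesis. Testing an absolute margin as its equivalent odds ratio is a choice of scale, and a common odds ratio may be the more stable measure across centres.

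A reader might also infer that the test exceeds its error rate. The document does not support that as a general statement. Pooling is the natural reading of a single incidence for the control cohort, but the text does not state it; with a standardised incidence the inflation disappears. Even with pooling, the level stays below 2.5% when every centre has the same control share. Inflation needs marked centre differences together with relatively more controls from low-incidence centres. With assumed incidences of 9, 9.5, 10.5 and 11%, the strong shift gives only 2.7%. Nothing in the document links control share to incidence.

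A still stronger reading would fix OR* at the planning incidence of 10%. The level would then be 6.0% at a true 12% and 11.2% at a true 14%. But the text derives OR* from the control cohort, so the point does not rest on this.

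Two parts of the objection do not hold. It could be said that a constant difference across centres favours the difference rule, but that rule also held its level (2.4% to 2.6%) when data were generated under a common odds ratio. And it could be said that the computation of OR* belongs in an SAP. The article itself, however, fixes the hypothesis, the test and the source of OR*, and leaves the size of the limit open.

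**Conclusion.** The point stands in limited form. The scales are reconciled by an explicit conversion, but the level for the 0.5-point margin is not fixed at 2.5%.

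- With an observed OR* treated as a constant, the test is mildly conservative, at about 2.1% to 2.2%. The loss of about 1 to 2 points of power matters because power is only about 75% at 50,000 per cohort, against the 80% sought.
- With a control incidence pooled over centres, the level follows the centre mix: about 1.6% to 2.7% for mild shifts and 1.2% to 4.5% for strong ones.

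The second range rests on assumed centre incidences of 6 to 14% and assumed mixes. The actual direction and size cannot be known from the document. The change should be made, but the finding is not that the planned test is invalid.

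**What to change.** State one primary rule on the scale of the margin: non-inferiority is declared if the upper limit of the two-sided 95% confidence interval for the centre-stratified Mantel-Haenszel risk difference (PBM minus control) is below 0.5 percentage points. Report the Mantel-Haenszel odds ratio with its interval as a secondary measure. OR* is then no longer needed.

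In the simulations this rule kept its level at 2.4% to 2.6% in every scenario. It also gained 1 to 2 points of power over an odds ratio test that uses a centre-standardised OR*.

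The cost is one sentence and no new data, since the interval for the difference is already planned. The small downside is that a risk difference may be less constant across centres than an odds ratio; reporting the odds ratio alongside covers this.

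If the odds ratio test is kept, the least that is needed is to state which control incidence defines OR* and to account for its sampling error.
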